### Inclusion criteria

2.3

1.adults aged 19 years or over but under 80 years;2.fulfillment of the DSM-5 diagnostic criteria for insomnia disorder^[1]^;3.total Insomnia Severity Index (ISI) score ≥15 points;4.patients with prehypertension (systolic blood pressure [SBP] 120 to 139 mm Hg or diastolic blood pressure [DBP] 80 to 89 mm Hg) or stage 1 hypertension (SBP 140–159 mm Hg or DBP 90–99 mm Hg), as defined in the seventh report of the joint national committee^[20]^;5.have voluntarily signed written informed consent forms approved by the institutional review board (IRB) after sufficient explanation about this study.

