### Interventions

2.7

Participants in the SYM group will receive 3.0 g SYM granules twice a day before or between meals for 4 weeks. The dosage is based on the regimen approved by the Korea Ministry of Food and Drug Safety. We will use Kracie Sihogayonggolmoryeo-tang Extract Fine Granules manufactured by Kracie Pharma Korea Co., Ltd (Seoul, Republic of Korea) in accordance with good manufacturing practice standards. The SYM granule is a light brown-brown mixture of the hot water extracts of 11 medicinal plants: *Bupleuri Radix* 5.0 g, *Fossilia Ossis Mastodi* 2.5 g, *Ostreae Testa* 2.5 g, *Scutellariae Radix* 2.5 g, *Cinnamomi Ramulus* 3.0 g*, Poria Sclerotium* 3.0 g*, Zingiberis Rhizoma Recens* 0.8 g, *Zizyphi Fructus* 2.5 g*, Rhei Radix et Rhizoma* 1.0 g*, Pinelliae Tuber* 4.0 g, and *Ginseng Radix* 2.5 g per 1 day. A pharmacist will be responsible for the storage, dispensation, and quality control of the SYM granules. If there are any adverse events during the study period, investigators will take appropriate action depending on the severity of the adverse event and the causal relationship with the investigational product.

The wait-list group will not receive SYM granules and will be instructed to maintain conventional care during the study period. The participants in this group will receive 2 weeks of SYM granules as compensatory treatment after the wait-list period if desired under the judgment of Korean medicine doctors, although this will not be included in the analysis. All participants in both groups will be educated and provided with brochures on maintaining sleep hygiene and hypertension lifestyle modification including diet and exercise during the study period.

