### Statistical analysis

2.10

All statistical analyses will be conducted by an independent statistician using SPSS Statistics for Windows, Version 24.0 (IBM Corp., NY, USA). According to the intention-to-treatment principle, which analyzes all participants who have been randomized, all data obtained from participants who undergo an outcome measurement at least once after randomization will be included in the effectiveness analysis. Per protocol set (PPS) analysis will also be conducted if necessary, including only participants who complete the entire process as described in the protocol with no significant violations. Safety analysis will include all data obtained from participants who take the investigational product at least once.

For each group, categorical data will be presented as frequency and percentage, and continuous data as mean and 95% confidence intervals or median according to the distribution of the data. Any statistical differences between 2 groups will be tested by using the Chi-Squared test or Fisher exact test for categorical data and using the Independent *t* test or Wilcoxon rank sum test for continuous data.

The primary outcome is the total ISI score at 4 weeks post-treatment. A two-sided test with a significance level of 0.5 will be performed using an analysis of covariance with the baseline as the covariate and the treatment group as fixed factors. In addition, the analysis can be performed by setting variables that show statistically significant differences in demographic or social characteristics or variables that can affect insomnia or blood pressure as covariates. The last observation carried forward method will be used for missing data. If necessary, subgroup analysis may be performed by categorizing the baseline characteristics of the participants at the screening visit or the baseline visit. Intra-group changes in the outcome measures from baseline to post-treatment will be analyzed using the Chi-square test or Fisher exact test for categorical data and the paired *t* test or Wilcoxon signed rank test for continuous data. Furthermore, we will use a mixed effect model to identify trend changes.

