Nevertheless, to the best of our knowledge, this is the first study evaluating the feasibility and effect of SYM on insomnia patients with prehypertension or stage 1 hypertension using validated questionnaires. Though hypertension itself is not a major problem, it can increase the risk of developing life-threatening cerebrovascular diseases.^[43]^ Insomnia disorder is also known to increase the risk of cardiovascular diseases.^[4]^ Therefore, we will evaluate the degree of atherosclerosis by measuring baPWV, ABI, hs-CRP, ESR, homocysteine, and fibrinogen as markers of cardio-cerebrovascular disease during the study period to investigate the effects of SYM on atherosclerosis. If the treatment effect and safety of SYM compared with the wait-list control is demonstrated through this pilot study, the findings are expected to provide a base for large-scale, confirmatory, multicenter, high-quality randomized control trials to draw definite conclusions regarding the efficacy and safety of SYM for patients with concurrent insomnia disorder and hypertension. Furthermore, the results may provide stronger evidence of SYM as a treatment option for insomnia disorder with hypertension for clinicians, patients, and researchers.

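### Baseline-adjusted ANCOVA is stated only for the ISI; continuous secondary outcomes get an unadjusted between-arm test, an unspecified mixed model and within-arm tests that do not estimate the SYM effect

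*Protocol article*

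**What the plan says.** Section 2.10 of the protocol article sets out four analyses.

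- **Primary outcome.** In the paragraph on the ISI score at 4 weeks, the model is an ANCOVA with "the baseline as the covariate and the treatment group as fixed factors". Extra covariates are optional. No sentence carries this model over to the secondary outcomes.
- **Between-group tests in general.** "Any statistical differences between 2 groups will be tested by using the Chi-Squared test or Fisher exact test for categorical data", and for continuous data an independent t "test or Wilcoxon rank sum test for continuous data". There is no baseline term, and the text does not say whether the test is on the week-4 value or on the change.
- **Within-arm tests.** "Intra-group changes in the outcome measures from baseline to post-treatment will be analyzed" by paired t or signed-rank test for continuous data. They are not labelled descriptive.
- **Mixed effect model.** It is added to look at trends. No outcome, group term or group-by-time contrast is named.

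On what both arms receive, section 2.7 says: "All participants in both groups will be educated and provided with brochures on maintaining sleep hygiene and hypertension lifestyle modification". The Discussion frames the trial as SYM against lifestyle modification only, and says the vascular and blood markers are measured "to investigate the effects of SYM on atherosclerosis".

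**The concern.** The trial asks a comparative question: what does SYM add to education and waiting? A paired test within the SYM arm asks only whether that arm changed over time. Section 2.7 gives both arms an intervention intended to improve sleep and blood pressure, so change over time is expected even if the granules are inert. A significant change in the SYM arm, or a significant SYM arm beside a non-significant wait-list arm, is therefore not evidence for SYM.

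The between-arm t or rank-sum test asks the right question. As written, however, it makes no stated use of baseline values that the trial collects for most of these outcomes, and with 12 to 15 per arm precision is scarce. Blood pressure and the atherosclerosis markers are central to the rationale, and the Discussion expects the pilot to provide a base for confirmatory trials. Estimates carried forward should be the between-arm ones, made as precise as the data allow.

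**Working it through.** **Inputs from the protocol.** Section 2.9 gives 12 evaluable per arm and 20% dropout: 12/(1 − 0.2) = 15 per arm, 30 in total, which reproduces the plan's figure. The plan states no effect size, SD or power, so there is no power figure to reproduce.

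**Assumptions.** Two-sided alpha is 0.05. Section 2.10 prints 0.5 ("A two-sided test with a significance level of 0.5 will be performed using an analysis of covariance"), which is a separate matter. Values are normal with equal SD at both times, and the baseline-to-week-4 correlation is r. The protocol gives no r, so a range is shown. Shared improvement is 0.25 or 0.5 SD; the true SYM effect for power is 0.8 SD.

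**1. Within-arm paired t test, no SYM effect.** The change has SD √(2(1 − r)), so for a shared shift c the noncentrality is c√n/√(2(1 − r)) on n − 1 df. Example: n = 15, c = 0.25, r = 0.5 gives 0.25 × 3.873/1 = 0.968, critical value 2.145, rejection 14.7%.

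| n per arm | shared shift | r = 0.3 | r = 0.5 | r = 0.7 | r = 0.8 |
|---|---|---|---|---|---|
| 15 | 0.25 SD | 12% | 15% | 21% | 30% |
| 15 | 0.5 SD | 33% | 44% | 64% | 81% |
| 12 | 0.25 SD | 10% | 12% | 18% | 24% |
| 12 | 0.5 SD | 27% | 35% | 53% | 70% |

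The arms are independent, so a significant SYM arm with a non-significant wait-list arm has probability p(1 − p). At 15 per arm and 0.25 SD this runs from 0.119 × 0.881 = 10% to 0.297 × 0.703 = 21%. At 0.5 SD it runs from 0.812 × 0.188 = 15% to 0.438 × 0.562 = 25%. Simulated between-arm ANCOVA stays at about 5%.

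**2. Between-arm power for a 0.8 SD effect.** The t test on week-4 values has noncentrality 0.8/√(2/15) = 2.191 on 28 df, critical value 2.048, power 56%. On change, the 0.8 is divided by √(2(1 − r)). ANCOVA leaves a fraction 1 − r² of the week-4 variance (0.91, 0.75 and 0.51 at r = 0.3, 0.5 and 0.7) and loses one df; its power was simulated.

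| n per arm | analysis | r = 0 | r = 0.3 | r = 0.5 | r = 0.7 |
|---|---|---|---|---|---|
| 15 | t, week-4 value | 56% | 56% | 56% | 56% |
| 15 | t, change | 32% | 43% | 56% | 78% |
| 15 | ANCOVA | 55% | 58% | 67% | 83% |
| 12 | t, week-4 value | 47% | 47% | 47% | 47% |
| 12 | t, change | 26% | 35% | 47% | 68% |
| 12 | ANCOVA | 45% | 48% | 55–56% | 72–73% |

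ANCOVA is the best of the three from r = 0.3 upward. At r = 0 it is slightly worse than the week-4 t test.

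**The case against.** Several stronger readings are tempting, and the document does not support them.

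- **That change is compared only within arms.** The primary ISI comparison is a baseline-adjusted between-arm ANCOVA, and the mixed effect model could yield a between-arm contrast of change. Its terms may well be set out in a fuller document. What stands is that the article names no such contrast for the secondary outcomes, while it does name the within-arm tests.
- **That the t and rank-sum tests certainly ignore baseline.** The text leaves open whether they use change. If they do, baseline enters, and at r = 0.7 the shortfall against ANCOVA is 78% to 83% rather than 56% to 83%. At r = 0.3 the change test is worse than the week-4 test.
- **That regression to the mean drives the within-arm results.** Entry requires "total Insomnia Severity Index (ISI) score ≥15 points" and raised blood pressure, so a reader might infer this. For ISI it inflates the paired test mainly if the qualifying screening score serves as baseline. The article distinguishes screening and baseline visits, and with a separate later baseline and equal correlations between visits the paired test stays near 5%. ISI is also the one outcome that already has the ANCOVA, and PSQI, baPWV, ABI and HADS are not entry criteria. The case here rests on the shared education alone.
- **That SYM's efficacy will be concluded from within-arm p-values.** No sentence says so; the Discussion speaks of comparison with the control.

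It is also fair that an unadjusted randomised comparison holds its nominal level, that this is a pilot without a power target, and that the gain depends on a correlation the protocol does not give. These points make the matter an improvement in precision and clarity, not the correction of an invalid test.

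**Conclusion.** The point holds in limited form. A baseline-adjusted between-arm analysis is stated only for the ISI. For continuous secondary outcomes, the named between-arm test carries no baseline term, the mixed model has no stated group contrast, and the within-arm tests do not estimate the SYM effect.

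At 15 per arm with no SYM effect, the within-arm test rejects in 12–30% of trials for a shared 0.25 SD improvement and in 33–81% for 0.5 SD, over r = 0.3–0.8. Compared with a t test on week-4 values, ANCOVA adds about 2, 11 and 27 points of power at r = 0.3, 0.5 and 0.7 for a 0.8 SD effect (58, 67 and 83 against 56). It adds nothing material below about r = 0.3. The shared shift, the correlation, the effect size, alpha 0.05 and normality are all assumed. The change is worth making because it uses the trial's own model and data already planned.

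**What to change.** In section 2.10:

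1. Extend the primary ANCOVA to each continuous secondary outcome that has a baseline measurement: week-4 value on treatment group and that outcome's own baseline. Use the screening value for hs-CRP, ESR, homocysteine and fibrinogen, which section 2.8.2 schedules at screening and 4 weeks. Report the adjusted between-arm difference with its 95% CI.
2. For clearly non-normal outcomes, use a log transform or a rank-based ANCOVA, so that a distribution-based option remains.
3. Keep the plain t or rank-sum test where no baseline exists, such as PGIC.
4. Report within-arm changes descriptively, as mean or median with 95% CI, and state that no SYM effect will be inferred from them.

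The cost is a few lines of text and one degree of freedom per model. No new measurements or participants are needed. The timing of EQ-5D-5L is given only in Table 1, which is not reproduced in the text at hand, so item 1 is limited to outcomes with a baseline value.

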### Trial design

2.1

A prospective, randomized, wait-list controlled, parallel, pilot clinical trial will be performed at the Daejeon Korean Medicine Hospital of Daejeon University (Daejeon, Republic of Korea). The trial period will include 4 weeks of medication (twice a day) and 2 weeks of follow-up. The study procedure is summarized in Figure 1 and Table 1. A total of 30 participants will be included and they will be randomly assigned to a SYM group or a wait-list group in a 1:1 allocation ratio. Participants will be informed about the objectives, procedures, and potential benefits, and risks of the trial through standardized interviews prior to their participation and informed consent will be obtained from all participants. Participants will be allowed to withdraw from the study at any time without negative consequences and will be immediately notified when new information regarding the study is obtained. The personal information of the participants will be de-identified and will be accessible only to the investigators involved in this study. This follows the Consolidated Standards of Reporting Trials (CONSORT) Extension for Chinese Herbal Medicine Formulas 2017^[21]^ and Standard Protocol Items: Recommendations for Interventional Trials (SPIRIT) 2013 statement.^[22]^ In addition, the trial will be conducted in accordance with the Declaration of Helsinki and Good Clinical Practice Guidelines.

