#### Primary outcomes

2.8.1

The primary outcome measure is the total ISI score and will be measured at all visits. The primary endpoint is 4 weeks after treatment. The ISI questionnaire is designed to screen for the diagnosis and severity of insomnia through 7 items corresponding to the symptoms of insomnia. The total score ranges from 0 to 28, with 0–7 indicating no clinically significant insomnia, 8–14 indicating subthreshold insomnia, 15–21 indicating clinical insomnia (moderate severity), and 22–28 indicating clinical insomnia (severe). We will use the validated Korean version of the ISI questionnaire in this study.^[25,26]^

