### Sample size

2.9

There has been no clinical trial to evaluate the effects of SYM on individuals with both insomnia disorder and prehypertension or stage 1 hypertension. Therefore, a formal sample size calculation was not performed because this study will evaluate the feasibility of subsequent confirmatory randomized controlled trials. With reference to a study that recommends a minimum of 12 participants per group in a pilot study in the biological science field,^[40]^ a total of 30 participants were deemed necessary for each group of 15, anticipating a 20% dropout rate.

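### Within-group changes in categorical outcomes are assigned tests for independent samples, although the before and after values come from the same participants

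*Protocol article*

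**What the plan says.** Statistical analysis (2.10) covers two kinds of comparison.

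- Between the arms: "Any statistical differences between 2 groups will be tested by using the Chi-Squared test or Fisher exact test for categorical data", with the independent t test or the rank sum test for continuous data.
- Within each arm: "Intra-group changes in the outcome measures from baseline to post-treatment will be analyzed using the Chi-square test or Fisher exact test for categorical data", followed by "the paired *t* test or Wilcoxon signed rank test for continuous data".

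So the continuous tests change from independent to paired versions when the comparison moves from between arms to within an arm. The categorical tests do not change. No paired categorical test is named anywhere in the article. The section also announces a mixed effect model for trends, as an addition to these tests and not in place of them.

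The primary analysis is separate: an ANCOVA of the total ISI score at 4 weeks, with baseline as covariate and treatment group as factor.

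**The concern.** A within-arm change uses two observations on each participant. The Chi-square and Fisher exact tests can be applied to such data in two ways, and neither answers the question asked.

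- **Stacked:** the baseline counts and the post-treatment counts are treated as two independent groups. The test then ignores who switched, and its variance is wrong unless the two observations are uncorrelated.
- **Cross-table:** baseline category is tabulated against post-treatment category. The null hypothesis is then that the two are unassociated. People who stay as they were produce strong association, and so a small p value, when nothing has changed.

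At stake are the within-arm p values for any outcome reported as a category before and after treatment. Candidates are the ISI severity bands, the PSQI cut-off above 5 and the EQ-5D-5L levels. Because the article names the tests, this is a misstated method and not a detail left for a later plan; an analysis that follows the text would inherit it.

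**Working it through.** **Inputs from the protocol.** Sample size (2.9) cites a study that "recommends a minimum of 12 participants per group in a pilot study" and allows 20% dropout. Its figure reproduces: 12 / (1 − 0.20) = 15 per group, 30 in total. The check therefore uses n = 15, with n = 12 as the number left after dropout.

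**Inputs assumed.** The protocol gives no category proportions and no within-person correlation (phi), so all counts, proportions and phi values below are assumptions. It gives no level for the within-group tests; two-sided 0.05 is used. (The level printed for the primary test, in "A two-sided test with a significance level of 0.5 will be performed", is a separate matter and is not used.)

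**Example 1: 12 of 15 fall to 6 of 15, with six switches one way and none back.**

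- Exact McNemar: 2 × 0.5^6 = 0.031.
- Stacked Fisher on [12, 3; 6, 9]: p = 0.060.
- Cross-table Fisher on [6, 6; 0, 3]: p = 0.229.
- Within-person correlation: (6×3 − 6×0) / √(12×3×6×9) = 18 / 44.1 = 0.41.

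**Example 2: 8 of 15 at both times and nobody changes.**

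- McNemar: no switches, p = 1.
- Stacked Fisher: p = 1.
- Cross-table Fisher on [8, 0; 0, 7]: p = 0.00016, for a change that did not occur.

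**Example 3: 10 of 15 fall to 6 of 15.**

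- Stacked Fisher on [10, 5; 6, 9]: p = 0.272 whatever the pairing.
- Exact McNemar: 2 × 0.5^4 = 0.125 for 4 switches against 0 (phi = 0.58), or 0.344 for 7 against 3 (phi = −0.29).

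**Why stacking is usually conservative.** With a common proportion p at both times, the true variance of the difference is 2p(1 − p)(1 − phi)/n. The stacked test uses 2p(1 − p)/n. At phi = 0.5 the variance it uses is 1/(1 − 0.5) = 2 times too large.

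**Rejection rates when there is no true change.** Exact enumeration of all paired 2×2 tables, n = 15, 50% at both times, with P(yes at both) = 0.25 + 0.25 × phi:

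| Test | phi = 0 | 0.3 | 0.5 | 0.7 |
|---|---|---|---|---|
| Stacked chi-square | 4.6% | 1.8% | 0.6% | 0.1% |
| Cross-table chi-square | 4.4% | 19% | 48% | 83% |
| Cross-table Fisher | 3.1% | 15% | 40% | 76% |
| McNemar, asymptotic | 4.4% | 5.0% | 4.3% | 1.8% |
| McNemar, exact | 1.8% | 1.0% | 0.4% | 0.05% |

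At phi = −0.3 the stacked chi-square rejects 7.8%. At n = 12 and phi = 0.5 the stacked chi-square rejects 1.0% and the cross-table chi-square 43%, so the pattern is the same.

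**Power for a true fall from 70% to 30%, phi = 0.4.** At n = 15, exact McNemar has 58.3% against 40.2% for stacked Fisher. At n = 12 they are level, at 33.5% and 34.3%. The case for the paired test is that it tests change on paired data, not that it always gains power.

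**The case against.** **The wording may be loose.** McNemar's statistic is referred to a chi-square distribution, so the test named could be meant as McNemar. This does not stand: Fisher's exact test is the stated alternative and is not a small-sample McNemar, the same pair of tests serves the between-group comparison, and only the continuous tests were switched to paired versions.

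**No affected outcome is identified.** This stands. The primary outcome is the total ISI score; its bands are given as interpretation, as in "The total score ranges from 0 to 28, with 0–7 indicating no clinically significant insomnia", and the PSQI cut-off is given in the same way. No level-by-level EQ-5D-5L analysis is stated. The PGIC rates improvement after treatment and so has no baseline. The remaining outcomes are mostly scores or measurements, for which the sentence gives suitable paired tests. The error may reach few outcomes, or none.

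**The counts are invented.** This also stands. They show how the tests behave and do not predict this trial's data.

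**Stronger readings a reader might infer.**

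- That the cross-table cannot be computed for ISI severity class because everyone enters at 15 or more. The ISI description (2.8.1) divides that range into moderate (15–21) and severe (22–28), so entry at 15 does not put everyone in one class. The table collapses to a single baseline row if ISI is split at 15, which is not a defined outcome, or if no entrant happens to score 22 or more.
- That stacking readily produces false positives. It does so only with negative within-person correlation, as in the 7-against-3 case, which is implausible for repeated sleep status. False positives for change come from the cross-table use, and the protocol does not say which use is meant.

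**Conclusion.** The sentence is wrong as written: it names tests for independent samples for paired categorical data, and its own continuous half shows that pairing was recognised. The size of the error depends on how the tests would be applied. With an assumed phi of 0.5, 50% margins and n = 15, stacking cuts a nominal 5% chi-square test to 0.6%, while the cross-table version rejects 48% of the time with no change at all.

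The consequence is limited. A p value could be invalid only for an outcome that is in fact analysed as a before-after category, and the protocol commits to none. The primary ANCOVA, the between-group tests, the sample size and the feasibility outcomes are untouched. In a 30-person pilot this is a minor but real error.

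**What to change.** Replace the categorical half of the within-group sentence. For outcomes with two categories, use the exact McNemar test, which suits 12 to 15 participants per arm. For ordered categories, use the marginal homogeneity test or the Wilcoxon signed-rank test. Leave the continuous half as it is.

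The cost is one changed sentence. The tests are available in SPSS, and no change to design, data collection or sample size is needed. One limit should be accepted: the exact McNemar test is itself conservative in arms this small. If all switches go one way, six are needed to fall below 0.05, since five give 2 × 0.5^5 = 0.0625.
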